## 2. Materials and Methods

### 2.1. Study Design and Setting

This study follows a quasi-experimental design involving two intervention schools undergoing schoolyard greening and two comparison schools without environmental changes. All participating schools are primary schools situated in the Province of Limburg of Belgium and The Netherlands (Figure 1). These provinces are characterized by a low SES, compared to the means of the countries [36,37]. ClinicalTrials.gov identifier (NCT number): NCT04898439. Baseline data collection was completed prior to the start of the intervention, with all baseline measurements conducted in November 2021.

School and subject recruitment. Two schools actively participate in the process of greening the schoolyard (one in Belgium and one in The Netherlands). Two other schools in the nearby region are control schools (one in Belgium and one in The Netherlands). Randomization was not possible due to the necessity for complete voluntary cooperation and participation of the intervention schools in greening the schoolyard. Because participation in the greening intervention required voluntary school commitment and alignment with construction timelines, randomization was not feasible. Therefore, potential confounders at both the child and school level will be measured and adjusted for in the linear mixed models. Baseline measurements were completed in November 2021 (T0). Follow-up measurements were planned each half-year for two years until November 2023 (T6: May 2022, T12: November 2022, T18: May 2023, and T24: November 2023). In The Netherlands, not all measurements could be taken due to practical reasons.

Intervention school recruitment. In early 2021, a newspaper call in The Netherlands recruited nine schools from Limburg to green and diversify their schoolyards. These schools were interviewed, and one was selected to participate as an intervention school on the basis of feasibility criteria and the comparability of the schoolyard size and characteristics. Selection of the Belgian intervention and control school was performed by the ‘Provinciaal Natuurcentrum Hasselt’ based on their call to green schoolyards and make schoolyards more biodiverse the comparableness of the schoolyards and number of enrolled students. The recruitment of the intervention schools was completed in September 2021.

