Control school recruitment. The schools that voluntarily agreed to participate were selected on the basis of the following inclusion/exclusion criteria: a high pavement-to-greenery ratio and a location in the proximity of the intervention schools with comparable populations and SES backgrounds.

Subject recruitment. Children were recruited for the baseline measurement through informational brochures sent via mail and reminders from the school staff. Furthermore, the research team visited all classrooms to provide information about the study and encourage participation. All children aged 7–12 from both intervention and control schools were eligible for inclusion in this study. Before the baseline examination, written consent from the parents was obtained and children gave their oral permission to participate. The enrollment of children for the initial measurement was concluded in November 2021.

Intervention. Both intervention schools underwent a greening procedure increasing biodiversity, in which they adjusted the gray schoolyard into a green biodiverse schoolyard consisting of (i) the creation of adventurous and diverse play areas, (ii) the establishment of green rest areas, (iii) the planting of flowers, shrubs, hedges and/or trees, and/or (iv) variation in activity zones such as farm animals, pools or vegetable gardens.

Because the greening intervention was implemented by two different schools and included varying components, such as water features, gardens, and diverse vegetation, some heterogeneity in intervention intensity is expected. As each country (Belgium and The Netherlands) includes one intervention and one control school, the correction for country as fixed factor captures unmeasured differences between schoolyards.

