### 2.9. Number of Participants

Due to the explorative nature of the study (hypothesis generating), no detailed sample size calculations are performed. The aim is to include 150–200 participating children from the participating schools in The Netherlands and Belgium. To account for missing data (assumed to be around 20%), the effective sample size for the analysis might vary between 80 and 120 children (40 to 60 per group). Based on 80% power and a significance level α of 0.05, standardized effect sizes (Cohen’s) between 0.52 and 0.63 can be detected with these expected sample sizes. This study was approved by the commission for Medical Ethics of Hasselt University (CME2021/042) and is a part of the original HPSF trial (METC-Z no. 14-N-142).

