### 2.10. Data Analysis

Linear mixed model analysis will be employed to evaluate the longitudinal impact of the intervention on the primary outcomes, absolute BMI Z-scores, change in cognitive function, change in well-being, and change in black carbon levels. Data will be analyzed using linear mixed models, performed in IBM SPSS Statistics for Windows (version 28.0.1.1, Armonk, NY, USA: IBM Corp). This approach addresses correlations within individuals inherent in repeated-measures research designs. Its advantage lies in handling missing values naturally through a likelihood-based method, assuming data are missing at random.

The fixed part of the model incorporates group (intervention vs. control), time (measurement time points), the interaction term group*time, and country (Belgium/The Netherlands). Baseline variables linked to missing data or outcomes will also be included for unbiased and precise results. To account for the correlation between repeated measurements several covariance structures (including random effects if necessary) will be considered. The best covariance structure for the repeated measurements will be chosen based on Akaike’s Information Criterion. The analysis will encompass all participants with at least one outcome measurement. Because several measurements were collected only in Belgian or only in Dutch schools, the resulting missingness is structured and not at random. Linear mixed models are used because they accommodate unbalanced data and allow all available observations to be included without listwise deletion. Country will be included as a fixed effect in all models to control for systematic differences between the Belgian and Dutch school contexts. For outcomes collected in only one country, analyses will be conducted within that specific subsample and reported separately. In addition, sensitivity analyses will be performed to examine whether excluding country-specific measures affects the direction or magnitude of findings for outcomes measured in both countries.

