No school-level random effects were added as the number of schools is limited to four (two in Belgium, two in The Netherlands). Since each country only includes one intervention and one control school, including country as fixed factor accounts for the school effect. Distinct statistical methods will address the other research inquiries. Longitudinal effects on numerical quantitative outcome variables will be evaluated employing the identical linear mixed models utilized for the primary outcome. Categorical outcome variables, on the other hand, will be scrutinized through a logistic mixed-model analysis technique (or generalizing estimating equations (GEE)), adopting a model akin to the one delineated for the primary study parameter.

To account for the correlation between repeated measurements several covariance structures (including random effects if necessary) will be considered. The model-fit will be evaluated using the −2log likelihood, where the best covariance structure for the repeated measurements will be chosen based on Akaike’s Information Criterion.

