A key advancement of this study is its ability to explore potential mechanisms underlying these health effects by integrating ecological, behavioral, cognitive, and environmental exposure data within a single protocol. Whereas most previous school-greening studies focused solely on behavioral or psychological outcomes, this study combines detailed biodiversity assessments, objective PA measurements, cognitive testing, and biomarkers of internal black carbon exposure. This multidimensional approach allows examination of whether increased biodiversity is associated with changes in cognitive functioning via restorative and stress-reduction pathways, and whether greener schoolyards may mitigate children’s internal exposure to airborne pollutants by altering microenvironmental conditions. By linking ecological features of the schoolyard to both cognitive and physiological markers, this study provides the opportunity to investigate mechanistic pathways that have rarely been tested empirically in school settings.

Though limited by its non-randomized design, the inclusion of schools from Belgium and The Netherlands enhances generalizability. A comprehensive set of outcome measures—anthropometric data, cognitive assessments, questionnaires, and activity monitoring—supports a robust analysis. Due to the modest sample size, the study is considered an exploratory study aimed at informing future, larger-scale research.

Challenges include school-specific logistical barriers, reliance on some self-reported data, and the need for long-term maintenance. Future studies should incorporate more objective data and extended follow-up periods.

While previous research has evaluated green schoolyards [58,59,60,61], the present study is distinguished by its focus on biodiversity and novel outcomes such as black carbon exposure and cognitive functioning. Comparisons with a comprehensive school health program that includes PA and nutrition [18] offer deeper insights into the potential of biodiverse schoolyards.

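### A country fixed effect does not account for the school effect: within each country school and intervention are confounded, and school-specific change enters the greening effect with child-level standard errors

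*Protocol article*

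**What the plan says.** Section 2.1 describes four non-randomised schools: in Belgium and in the Netherlands, one school that greens its yard and one control. It expects the greening to differ between the two intervention schools and then states that "the correction for country as fixed factor captures unmeasured differences between schoolyards". It also says that "potential confounders at both the child and school level will be measured and adjusted for in the linear mixed models".

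Section 2.10 gives the model: "The fixed part of the model incorporates group (intervention vs. control), time (measurement time points), the interaction term group*time, and country (Belgium/The Netherlands". The correlation structure covers repeated measurements on the same child. School random effects are left out because there are only four schools, with the added reason: "Since each country only includes one intervention and one control school, including country as fixed factor accounts for the school effect".

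Section 2.9 gives detectable effects of 0.52 to 0.63 for 80 to 120 analysed children, with no allowance for school. Under Table 1, there are no Dutch measurements at T6 and T24, and some outcomes exist in one country only (black carbon in Belgium; sleep, absenteeism, parental PedsQL and food items in the Netherlands). Section 2.10 analyses one-country outcomes within that country.

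**The concern.** Country is what the two schools of a pair have in common, so adjusting for it cannot remove a difference between them. The effect of interest is group-by-time, a contrast of within-child changes, and a term that is constant over time should largely cancel from it.

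If so, two things follow. A change of staff, meals or neighbourhood at one school during follow-up is reported as an effect of greening. And the standard errors treat children of one school as independent, although the intervention was given to whole schools. A reader who accepts the stated reason would believe that both problems had been dealt with.

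**Working it through.** **1. What country can identify.** Four schools carry 4 − 1 = 3 between-school degrees of freedom. Group uses one and country one. The third, country by group, is the difference between the two school pairs. It is not in the model, yet it is the heterogeneity that Section 2.1 expects.

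**2. Does country alter group-by-time?** Four-school data were simulated and fitted by generalised least squares with a random child intercept (within-child correlation of 0.8 assumed). Estimates, with standard errors in brackets:

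| Data | Contrast | No country term | With country | School fixed effects |
|---|---|---|---|---|
| Equal schools, T0/T12/T18 complete | T12 | 0.1058 (0.1265) | 0.1058 (0.1265) | 0.1058 (0.1265) |
| Unequal schools, complete | T12 | 0.3556 (0.1271) | 0.3556 (0.1271) | 0.3556 (0.1271) |
| Unequal schools, no Dutch T6/T24 | T12 | 0.1914 (0.1271) | 0.1914 (0.1271) | 0.1914 (0.1271) |
| Same | T18 | 0.2175 (0.1271) | 0.2175 (0.1271) | 0.2175 (0.1271) |
| Same | T6 | 0.2478 (0.1655) | 0.2290 (0.1656) | 0.2397 (0.1662) |
| Same | T24 | 0.0570 (0.1655) | 0.0382 (0.1656) | 0.0489 (0.1662) |

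The country term changes nothing at T12 and T18. At T6 and T24 it moves the estimate by 0.2478 − 0.2290 = 0.019, about a tenth of a standard error.

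**3. Where only one country contributes.** For black carbon and the Dutch-only outcomes, country is a constant and drops out: the comparison is one school against one school. For BMI z-score at T24, the only T24 measurements come from one Belgian school per arm, and country cannot separate those two schools.

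**4. The plan's own precision figure.** Section 2.9 gives its basis as "Based on 80% power and a significance level α of 0.05". For independent children, the detectable effect is (1.960 + 0.842) × √(2/n): 0.626 at n = 40 per group and 0.511 at n = 60. The noncentral t gives 0.634 and 0.516, against the stated 0.63 and 0.52. The figure is reproduced, and it assumes no school-level variation.

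**5. Size of the effect on inference.** Inputs: 80 to 120 analysed children over 4 schools (Section 2.9), so m = 20 to 30 per school. The ICC is the share of variance in change due to school. The article gives none, so a range is assumed. Design effect DE = 1 + (m − 1) × ICC; true two-sided type I error = 2 × [1 − Φ(1.96/√DE)]; detectable effect = normal-approximation value from step 4 × √DE.

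| ICC | DE (m = 20; 30) | Type I error | Detectable effect |
|---|---|---|---|
| 0.005 | 1.095; 1.145 | 6.1%; 6.7% | 0.66; 0.55 |
| 0.01 | 1.19; 1.29 | 7.2%; 8.4% | 0.68; 0.58 |
| 0.02 | 1.38; 1.58 | 9.5%; 11.9% | 0.74; 0.64 |
| 0.05 | 1.95; 2.45 | 16.0%; 21.1% | 0.87; 0.80 |

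Example, ICC 0.05 and m = 30: DE = 1 + 29 × 0.05 = 2.45; 1.96/√2.45 = 1.252; two-sided tail 21.1%. Simulation with 20,000 replicates agrees: 7.4% and 8.4% at 0.01, 9.4% and 12.1% at 0.02, 16.2% and 21.4% at 0.05. Adding country-by-time does not help: 16.6% and 21.6% at 0.05.

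These figures concern child-level outcomes. They do not carry over to black carbon, for which Section 2.8 pools urine by grade.

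**The case against.** The study is declared exploratory, and the Discussion concedes non-randomisation, possible confounding and a modest sample. With two schools per arm no school-level test is realistic, so omitting school random effects is defensible. Conditional on these four schools, child-level intervals are a legitimate summary. The inflation rests on an assumed ICC and nearly vanishes at small values. All of this stands. None of it supports the statement that school has been accounted for, and none of the caveats says that school and intervention cannot be separated within a country or that the standard errors ignore clustering.

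Some stronger readings are tempting but not supported:

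- A reader might infer that the country term never affects group-by-time. That is exact only with complete data; the planned missing Dutch waves allow a small shift at T6 and T24.
- A reader might infer that school-level adjustment, as promised in Section 2.1, is impossible. One degree of freedom is left, so one time-constant school covariate could be fitted, and time-varying school factors are not bound by that count. Adjustment is severely limited, not ruled out.
- A reader might use more children per school and obtain more inflation. The analysed size that the plan states is 80 to 120, hence 20 to 30 per school.
- A reader might want the Discussion's remark that "the inclusion of schools from Belgium and The Netherlands enhances generalizability" withdrawn. It is a comparative remark and can stand beside a plain statement of what the intervals cover.

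**Conclusion.** The concern holds. Both statements about the country term are wrong, in Section 2.1 and in Section 2.10. The reasoning in steps 1 to 3 needs no assumed ICC: country does not separate the schools of a pair, and it leaves the main contrast unchanged or nearly so. School-specific change is therefore part of the estimated greening effect.

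The size is conditional. For inference beyond these four schools, a nominal 5% test has a true error of about 7-8%, 10-12% or 16-21% at an ICC of change of 0.01, 0.02 or 0.05, with 20 to 30 children per school; at 0.005 it is 6-7%. A reader might infer that the planned intervals are invalid outright or that school random effects were required. Neither follows. What fails is the stated reason that school is handled, and any reading of the intervals as evidence about greening at other schools.

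**What to change.** 1. Delete the two statements in Sections 2.1 and 2.10. Say instead that school and intervention are confounded within each country.
2. For outcomes and time points measured in both countries (T12 and T18 for BMI z-score), report the intervention-control difference in change separately by country, with the unweighted mean of the two and their difference. Use country-specific models, or country, group and time with all interactions. A separate four-level school factor is not needed and would be collinear with group. Report T6, T24 and one-country outcomes as single school-pair comparisons, since country-specific effects cannot be estimated where there are no Dutch data.
3. State that child-level intervals and p-values are conditional on these four schools.
4. Add a sensitivity interval with the variance multiplied by 1 + (m − 1) × ICC, over an assumed range such as 0.005 to 0.05. At m = 20 to 30 this widens intervals by a factor between √1.095 = 1.05 and √2.45 = 1.57.
5. In Section 2.1, state that at most one time-constant school-level covariate can be fitted and that, as a main effect, it would not correct group-by-time.

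The cost is some rewording, one extra table, wider sensitivity intervals and a more modest conclusion. No new data are required.

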## 3. Discussion

The Green Healthy Elementary School of the Future initiative addresses rising childhood obesity rates and the benefits of early exposure to green environments.

In this quasi-experimental study, the effects of transforming schoolyards into biodiverse green spaces on children’s physical and mental health, cognitive development, and well-being are examined.

There is strong evidence linking green spaces to better cognitive performance in children, including improved attention, academic outcomes, and stress reduction [50]. Exposure to nature is associated with lower risks of mental disorders in urban populations [51], supported by the Attention Restoration Theory (ART) and Stress Recovery Theory (SRT), which explain how nature reduces cognitive fatigue and stress [21,22,23].

An increase in schoolyard biodiversity is achieved through the intervention, which is associated with health benefits [22,23,24,25], supporting the biodiversity hypothesis: exposure to diverse species may enhance immune function through microbial diversity [26,27,28,29,30]. The biophilia hypothesis suggests that humans are naturally drawn to nature, benefiting their health [52,53,54], while the dilution effect hypothesis posits that biodiversity can reduce disease transmission [55,56,57].

By encouraging active, nature-based play, an increase in PA is promoted, and may reduce obesity risk. Previous studies link green spaces to increased PA and healthier BMI in children [58,59,60,61]. The socio-ecological design integrates natural elements to foster imaginative play and improve social behavior.

A key advancement of this study is its ability to explore potential mechanisms underlying these health effects by integrating ecological, behavioral, cognitive, and environmental exposure data within a single protocol. Whereas most previous school-greening studies focused solely on behavioral or psychological outcomes, this study combines detailed biodiversity assessments, objective PA measurements, cognitive testing, and biomarkers of internal black carbon exposure. This multidimensional approach allows examination of whether increased biodiversity is associated with changes in cognitive functioning via restorative and stress-reduction pathways, and whether greener schoolyards may mitigate children’s internal exposure to airborne pollutants by altering microenvironmental conditions. By linking ecological features of the schoolyard to both cognitive and physiological markers, this study provides the opportunity to investigate mechanistic pathways that have rarely been tested empirically in school settings.

Though limited by its non-randomized design, the inclusion of schools from Belgium and The Netherlands enhances generalizability. A comprehensive set of outcome measures—anthropometric data, cognitive assessments, questionnaires, and activity monitoring—supports a robust analysis. Due to the modest sample size, the study is considered an exploratory study aimed at informing future, larger-scale research.

Challenges include school-specific logistical barriers, reliance on some self-reported data, and the need for long-term maintenance. Future studies should incorporate more objective data and extended follow-up periods.

While previous research has evaluated green schoolyards [58,59,60,61], the present study is distinguished by its focus on biodiversity and novel outcomes such as black carbon exposure and cognitive functioning. Comparisons with a comprehensive school health program that includes PA and nutrition [18] offer deeper insights into the potential of biodiverse schoolyards.

Several limitations should be considered. First, the non-randomized design restricts the ability to infer causality and introduces potential confounding. Second, sample size limitations reduce statistical power and restrict subgroup analyses. Third, some measurements, particularly dietary behavior and well-being, rely partly on self-report, which may introduce reporting bias. Additionally, variations in data collection between countries (e.g., missing time points in The Netherlands) may lead to differences in data completeness.

Future research should aim to employ randomized or matched cohort designs, increase sample sizes, and include longer-term follow-up to evaluate sustained effects. Incorporating more objective measurements (e.g., continuous activity monitoring, environmental sensors, biological markers) will strengthen the evidence base. Future studies could also explore differential effects by socioeconomic status, baseline nature affinity, or schoolyard design features.

Study findings will be disseminated through peer-reviewed scientific publications, presentations at public health and environmental health conferences, and reports to participating schools and local authorities. Results will also be communicated to stakeholders involved in school policy, urban planning, and environmental education to support evidence-based decisions and promote the integration of biodiverse schoolyards into broader health-promotion strategies.

